# **STUDY DESIGN**

## **5 Study objectives**

### **5.1 Primary objectives**

- To investigate the safety and tolerability of a 4-plasmid DNA prime followed by an Ad5 boost with the boost administered IM, ID, or SC.
- To compare ID vs. IM and SC vs. IM routes of Ad5 boost administration to determine if either the ID or SC route is superior to IM in eliciting vaccine-induced HIV-specific T-cell responses as assessed by the magnitude of IFN- $\gamma$  ELISpot responses 4 weeks after the Ad5 boost.

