## **7.2.2 Cellular immunogenicity studies at HVTN and the NIAID Vaccine Immune and T-Cell Antibody Laboratory (NVITAL)**

Both the HVTN and VRC will evaluate cellular immunogenicity. The data from NVITAL will contribute to the data package that the VRC will use to determine whether the products and alternate routes of administration qualify for further evaluation. The data from the HVTN laboratory will be used for independent analysis, to evaluate how these vaccines compare to other vaccines, and in determining the HVTN's involvement in additional trials with these products.

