#### 8.4.2 Sample size calculations for immunogenicity

The main goal of this trial regarding immunogenicity is to determine if ID or SC route of administration of the Ad5 boost is superior to IM administration in eliciting vaccine-induced HIV-specific T cell responses. Because IM administration is easier to administer, IM administration would continue to be used with this product unless there is a large improvement in immune response. The immunogenicity outcomes involve both preliminary estimation and a formal comparison of the mean magnitude of T-cell responses among study groups. Since the standard error of the estimated mean response magnitude depends on the true population variance, several parameters for the sample size calculations for immunogenicity will be estimated from existing ELISpot assay data.

It has been observed from previous HVTN studies that the magnitude of T-cell responses assessed by the IFN- $\gamma$  ELISpot assay appears to be normally distributed after a logarithm transformation. Since logarithm transformations are more intuitive for interpreting fold differences, log-10 transformation will be adopted in the estimation of distribution parameters of the true underlying population distribution.

Consider the sample standard deviation to be 0.35 after log-10 transformation. Two-sided confidence intervals for the mean magnitude of the T-cell responses based on observing a particular mean magnitude of responses can be found in Table 8-3 for groups of size 30 and 27, accounting for 10% missing immunogenicity data.

**Table 8-3 Two-sided confidence intervals for the T-cell response based on observing a particular mean response magnitude in the vaccinees (n=30,27)**

| Observed mean magnitude* | 95% CI (n=30) | 95% CI (n=27) |
|--------------------------|---------------|---------------|
| 100                      | [75,134]      | [74,136]      |
| 150                      | [113,201]     | [111,204]     |
| 200                      | [150,267]     | [148,272]     |
| 250                      | [188,334]     | [185,339]     |
| 300                      | [225,401]     | [222,407]     |
| 350                      | [263,467]     | [259,475]     |
| 400                      | [300,534]     | [296,543]     |
| 450                      | [338,601]     | [333,610]     |
| 500                      | [375,668]     | [369,678]     |

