\*Observed SFU per ELISpot well ( $\sim 2 \times 10^5$  PBMC). Response rates conventionally reported per  $10^6$  PBMC.

A formal comparison of the immunogenicity between the study groups (n=30) will also be performed. For example, a 2-fold difference in mean response magnitudes between two groups of size 30 is detectable with 82% power for a two-sided two-sample t-test with a Type I error rate of 0.05. Based on groups size of 30 and a sample standard deviation of 0.35 after log-10 transformation, additional power calculations for comparison of mean response magnitudes between arms that can be distinguished with statistical power of 80% and 90% are provided in Table 8-4. This calculation accounts for 10% of enrolled participants having missing data for the primary immunogenicity endpoints. Note that the sizes of differences that the trial is powered to detect are fairly large.

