## 8.5 Statistical analysis

All data from enrolled participants will be analyzed according to the initial randomization assignment regardless of how many vaccinations they received. Since enrollment is concurrent with receiving the first vaccination, all participants will have received one vaccination and therefore will provide some safety data. The analysis is not strictly intent-to-treat but is approximately so; that is, individuals who are randomized but not enrolled do not contribute data and hence are excluded. Because of the brief length of time between randomization and enrollment—typically no more than 4 working days, according to the *HVTN Manual of Operations (HVTN MOP) (Study Operations >Enrollment >Randomization)*—very few such individuals are expected.

If a participant receives the wrong randomization assignment, analyses for immunogenicity will be done both according to the assignment they should have received and also according to the assignment they actually received. It is expected that there should be very few such cases.

Analyses for primary endpoints will be performed in SAS. All other descriptive and inferential statistical analyses will be performed using SAS, S-Plus, and/or R statistical software.

No formal multiple comparison adjustments will be employed for safety endpoints or secondary immunogenicity endpoints. However, multiple measurements of a specific type of immune response may be treated as a collection of hypotheses that requires a multiplicity adjustment. For example, determination of cellular immune responses to several different HIV-1 peptide pools as measured by the IFN- $\gamma$  ELISpot assay may entail a multiplicity adjustment to account for the multiple peptide pools considered.

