#### **8.5.4 Immunogenicity analysis**

For the statistical analysis of immunogenicity endpoints, all data from enrolled participants will be used according to the initial randomization assignment regardless of how many injections they received. The only exception will be to exclude data from HIV-infected

participants at or post infection. Thus, for HIV-infected participants, only immunogenicity data from samples drawn prior to HIV infection will be included in the analysis.

If assay data are qualitative (i.e., positive or negative), then analyses will be performed by tabulating the frequency of positive response for each assay by arm at each time point that an assessment is performed. Binomial response rates will be presented with their corresponding exact 95% confidence interval estimates.

To compare the response rates of any two vaccine arms, a significant difference will be declared if the 2-sided 95% confidence interval for the difference in response rates between the two arms excludes 0. If assays are run at multiple time points, the probability of observing at least one positive response by a given time point and the probability of observing more than one response by a given time point will be estimated, with corresponding confidence intervals, for each vaccine arm using maximum likelihood based methods [53]. Missing responses will be assumed to be missing at random (i.e., conditional on the observed data the missingness is independent of the unobserved responses).

For continuous assay variables, overall differences between arms at a specific time point will be tested by a 2-sample t-test if the data appear to be normally distributed after certain power or logarithm transformations, or by utilizing the nonparametric Wilcoxon rank sum test if the transformed data are not normally distributed. More sophisticated analyses employing repeated measures methodology (for example, repeated measures ANOVA or generalized estimating equations) may be utilized to incorporate immune responses over several time points. However, inference from such analyses would be limited by the small sample size of this study. All statistical tests will be 2-sided and will be considered statistically significant if  $p \leq 0.05$ . Graphical descriptions of the longitudinal immune responses will also be given.

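### The two primary route comparisons are each tested at two-sided 0.05 with no stated adjustment, and the protocol's power figures fit 0.025 per comparison rather than the 0.05 it states

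*Protocol*

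**What the plan says.** Protocol section 5.1 sets two comparisons, ID vs IM and SC vs IM, "to determine if either the ID or SC route is superior to IM in eliciting vaccine-induced HIV-specific T-cell responses", judged on IFN-γ ELISpot magnitude 4 weeks after the Ad5 boost. Success on one route is enough.

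Section 8.5.4 gives one rule for all tests: "All statistical tests will be 2-sided and will be considered statistically significant if" p ≤ 0.05.

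On multiplicity, section 8.5 says: "No formal multiple comparison adjustments will be employed for safety endpoints or secondary immunogenicity endpoints". For ELISpot readings on several peptide pools, it says the analysis "may entail a multiplicity adjustment to account for the multiple peptide pools considered". It says nothing about the two primary route comparisons.

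Section 8.4.2 gives the sizing inputs: "Consider the sample standard deviation to be 0.35 after log-10 transformation", 10% of participants without primary immunogenicity data, and "a 2-fold difference in mean response magnitudes between two groups of size 30" being "detectable with 82% power for a two-sided two-sample t-test with a Type I error rate of 0.05". Table 8-4 lists minimum detectable means at 80% and 90% power. The text states that the calculation allows for the 10% loss.

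**The concern.** There are two chances to meet one objective, each at the full 0.05, so the error rate for the objective as a whole exceeds that of a single test. Silence on the primary comparisons in section 8.5 leaves the blanket rule of section 8.5.4 in force.

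The planning figures also appear to have been computed at a different level from the one written beside them. If so, the protocol plans at one alpha and analyses at another, and its stated power and detectable differences cannot be taken at face value. Section 1 says the trial's data are to show which route boosts best, so the error rate and power of these two tests matter to how the result is used.

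**Working it through.** **Inputs.** From section 8.4.2: SD 0.35 on the log10 scale; 2-fold difference δ = log10(2) = 0.301; 30 per arm enrolled; 10% missing, so 30 × 0.9 = 27 evaluable; two-sided two-sample t-test; stated alpha 0.05; stated power 82%. From section 5.1: two comparisons against the same IM arm.

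**1. Reproducing the 82%.** Standard error of the difference: SE = 0.35 × √(2/n). Normal-approximation power: Φ(δ/SE − z), with z = 1.960 for alpha 0.05 and 2.241 for alpha 0.025. The exact figure uses the noncentral t distribution.

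| n per arm | SE | δ/SE | alpha | power, normal | power, exact t |
|---|---|---|---|---|---|
| 30 | 0.0904 | 3.331 | 0.05 | 91.5% | 90.6% |
| 27 | 0.0953 | 3.160 | 0.05 | 88.5% | 87.3% |
| 27 | 0.0953 | 3.160 | 0.025 | 82.1% | 80.0% |

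At the stated 0.05 neither sample size gives 82%. At 0.025 with 27 per arm, the normal approximation does: Φ(3.160 − 2.241) = Φ(0.919) = 82.1%.

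**2. Which alpha Table 8-4 uses.** Under the normal approximation the log fold difference is SE × (z_alpha + z_power). The ratio of the 90% to the 80% value therefore depends on alpha only, not on n or SD.

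- Expected at 0.05: (1.960 + 1.282)/(1.960 + 0.842) = 1.157.
- Expected at 0.025: (2.241 + 1.282)/(2.241 + 0.842) = 1.143.
- Table, arm-500 row: log10(1045/500)/log10(953/500) = 0.3201/0.2801 = 1.143.

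Across all rows the ratio runs from 1.139 to 1.143, the spread coming from rounding. The table matches 0.025.

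**3. Which n Table 8-4 uses.** Arm-500 row, 500 × 10^(SE × (z_alpha + z_power)), SD 0.35:

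| alpha | n per arm | 80% power | 90% power |
|---|---|---|---|
| 0.05 | 30 | 896 | 982 |
| 0.05 | 27 | 924 | 1018 |
| 0.025 | 30 | 950 | 1041 |
| 0.025 | 27 | 983 | 1083 |
| Table 8-4 | | 953 | 1045 |

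The closest fit is 0.025 with 30 per arm. An SD of 0.352, which rounds to 0.35, reproduces 953 and 1045. So the 82% fits 27 per arm, while the table fits 30.

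**4. Error rate of the either/or objective.** With equal arms and a shared control, the two test statistics correlate at (σ²/n)/(2σ²/n) = 0.5. Using a bivariate normal with that correlation:

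| level per comparison | any false significant difference: P(\|Z1\| > z or \|Z2\| > z) | false superiority only: P(Z1 > z or Z2 > z) |
|---|---|---|
| 0.05 | 9.1% | 4.5% |
| 0.025 | 4.6% | 2.3% |

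For reference, one comparison at two-sided 0.05 gives 5% and 2.5%. A Dunnett critical value of 2.212 corresponds to a level of 0.027 per comparison.

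**The case against.** **The false superiority rate is below 5%.** A reader might take 9.1% as the chance of wrongly declaring a new route better. It is not: 9.1% includes results in which ID or SC is significantly worse than IM. False superiority alone is 4.5%. This objection stands and limits the size of the point. Even so, 4.5% is nearly twice the 2.5% that a two-sided 0.05 test allows in one direction.

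**The peptide pools could push the error above 30%.** A reader might infer this, since section 7.2.2.1 reports responses by pool and any pool adjustment is optional. The documents do not support a figure. They give no number of pools for this trial, and section 8.5 foresees an adjustment. Assuming six pools (the number in Table 3-2, from an earlier Ad5 trial), one laboratory and no adjustment, the any-direction rate runs from 19% (pool correlation 0.9) to 44% (independent pools), and false superiority from 9.5% to 24%. These are scenarios. How pools are combined is commonly settled in a statistical analysis plan.

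**Two laboratories give two chances.** Section 7.2.2 says "Both the HVTN and VRC will evaluate cellular immunogenicity", and a reader might treat the two data sets as interchangeable routes to the primary claim. Section 7.2.2 gives them different uses, Appendix B classes NVITAL as a non-HVTN laboratory, and section 8.5.6 ties the primary-visit analysis to testing by the HVTN Laboratory Program. This reading falls.

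**The planners probably allowed for two comparisons.** That is a fair inference from the 0.025 fit, and section 8.5 does not rule out adjustment for the primary endpoint. But the only levels written down are 0.05 in section 8.4.2 and 0.05 for every test in section 8.5.4. An intended split would have to be stated.

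**It is a Phase Ib trial with a demanding practical standard.** Section 8.4.2 says IM would remain in use unless the gain is large, so p ≤ 0.05 alone does not decide the route. This tempers the consequences but does not correct the power figure or supply the missing level.

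**Conclusion.** The point holds in two parts.

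First, the either/or primary objective is tested twice at two-sided 0.05 with no stated adjustment. The familywise rate is 9.1% for any false route difference and 4.5% for false superiority, about double the rates at 0.025 each. This assumes equal arm sizes and one ELISpot variable.

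Second, the stated 82% power is not what alpha 0.05, SD 0.35 and 27 per arm give; the correct figure is 87% to 88%. The 82% and Table 8-4 both fit two-sided 0.025, but at different sample sizes (27 and 30), so the table appears to omit the stated 10% loss. The mismatch is arithmetic; that a Bonferroni split was intended is inference.

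The documents do not support a claim that the error rate exceeds 30%, or that the primary laboratory is left entirely open.

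**What to change.** - **Section 8.5.4:** state that ID vs IM and SC vs IM on the primary endpoint are each tested at two-sided 0.025, or by Holm or Dunnett at a familywise 0.05. Limit the general p ≤ 0.05 rule to other tests.
- **Section 8.5:** add the primary comparisons to the multiplicity paragraph.
- **Section 8.4.2:** state the 0.025 level, give power for a 2-fold difference as about 80% (exact t, 27 per arm), and recompute Table 8-4 at 27 per arm. By normal approximation the arm-500 row becomes about 983 and 1083.
- **Supporting step, sections 8.3.2 and 7.2.2:** name one ELISpot summary over pools, from the HVTN laboratory, as the primary variable, and label pool-specific and NVITAL results secondary. Do this before the immunogenicity analysis that section 8.5.6 permits ahead of study end.

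**Cost:** a few sentences and one recalculated table. Exact-t power for a 2-fold difference is 80.0% rather than the 87.3% that 0.05 would give, close to the 82% already quoted. The sample size of 90 need not change.

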#### **8.5.4.1 Missing data**

If the probability of missing immunogenicity measurements depends on either covariates or on the immunogenicity outcomes of participants, then the methods described above may give biased inferences and point estimates. If a substantial amount of immunogenicity data is missing (at least 1 value missing from more than 20% of participants), then secondary analyses of the immunogenicity endpoints will be conducted using methods that relax the missing completely at random assumption to a missing at random assumption. For a univariate binary and quantitative outcome, respectively, a generalized linear model with a

binomial or normal error distribution will be used for estimation and testing. For assessing repeated immunogenicity measurements, generalized estimating equations models with multiple imputation of missing responses will be used. The models will include as covariates all available baseline predictors of the missing outcomes. The longitudinal models will also include all observed immunogenicity data.

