### **7.2.2.1 IFN-gamma ELISpot**

Ex vivo T-cell responses will be assessed by IFN- $\gamma$  ELISpot using cryopreserved PBMC stimulated overnight with synthetic peptide pools that correspond to the proteins encoded by the vaccine constructs. ELISpot assays will be performed with specimens collected at baseline and at visits indicated in Appendix B. Responses will be reported as number of spot forming cells (SFC) per  $10^6$  cells/well recognizing any specific peptide pool.

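### The missing-data model that naturally covers the D196 ELISpot endpoint conditions on baseline predictors only; let the missing-at-random analysis of D196 use the observed D70 response as well

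*Protocol*

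**What the plan says.** Protocol section 8.5.4.1 (Missing data) applies when at least one immunogenicity value is missing from more than 20% of participants. It then calls for secondary analyses using "methods that relax the missing completely at random assumption to a missing at random assumption". Two routes follow:

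- **One outcome per participant, binary or continuous:** a generalized linear model is fitted, and its "binomial or normal error distribution will be used for estimation and testing".
- **Repeated measurements:** "generalized estimating equations models with multiple imputation of missing responses will be used".

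On conditioning, the section says "The models will include as covariates all available baseline predictors of the missing outcomes". It then adds, for one of the two routes only, "The longitudinal models will also include all observed immunogenicity data".

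Section 8.5.4 explains missing at random in the usual way: "conditional on the observed data the missingness is independent of the unobserved responses".

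The primary immunogenicity endpoint (sections 5.1 and 8.3.2) is ELISpot magnitude at one time point, four weeks after the Ad5 boost, which is D196. On sampling, section 7.2.2.1 states "ELISpot assays will be performed with specimens collected at baseline and at visits indicated in Appendix B". Appendix B puts those draws at D0, D70 and D196. D70 falls two weeks after the third DNA prime, which is the same in all groups, and before the boost at D168.

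**The concern.** The primary endpoint is one quantitative value per participant, so the natural reading of section 8.5.4.1 sends it to the univariate model. That model is fitted to participants whose D196 value is present and adjusts for baseline variables only. A participant with a D70 value but no D196 value contributes nothing about the immune response, although missing at random in the sense of section 8.5.4 allows loss to depend on that D70 value.

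Participants are HIV-uninfected and have no previous HIV vaccine exposure, so D0 ELISpot should say little about how strongly they respond. D70 is the only measured T-cell response to the prime before the boost.

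This analysis is meant to show whether the t-test result survives substantial missing data. If loss is related to the prime response, and the relation differs by route, it would carry the same bias as the complete-case comparison and could appear to confirm it.

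**Working it through.** **Conditioning sets side by side**

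| Analysis in 8.5.4.1 | Conditions on | Valid when missingness depends on |
|---|---|---|
| Univariate generalized linear model | arm, baseline predictors | arm and those predictors |
| Estimating equations with multiple imputation | arm, baseline predictors, all observed immune data (so D70) | any of these |

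The first is a genuine relaxation of missing completely at random, but narrower than missing at random given all observed data. The section states no figure that could be reproduced, so the remaining question is size.

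**Inputs from the Protocol:** 30 per group; SD 0.35 log10 (8.4.2); two-sided 0.05; trigger above 20% (8.5.4.1).

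**Assumed, because the documents give no value:** correlation ρ between D70 and D196 of 0.3, 0.5 or 0.7; 25% of D196 values missing in each arm; logit of the missingness probability changing by 0 or ±1 per SD of D70; a baseline covariate correlated 0 or 0.3 with D70. True route difference 0.

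**Analytic check of one arm mean** (baseline covariate uninformative). With missingness probability p and logit slope 1, the mean D70 among those observed shifts by −E[p(1−p)]/(1−0.25). Numerical integration gives E[p(1−p)] = 0.160, so the shift is −0.160/0.75 = −0.213 SD. The bias in the D196 mean is 0.35 × ρ × (−0.213):

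- ρ = 0.3: −0.022 log10
- ρ = 0.5: −0.037 log10
- ρ = 0.7: −0.052 log10

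**Simulation**, 3,000 trials per scenario, normal linear model with arm and the baseline covariate. Monte Carlo error is about 0.002 log10 for bias and √(0.05 × 0.95/3000) = 0.004 for type I error.

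| Dependence of loss on D70 | Bias in route contrast (log10) | Type I error |
|---|---|---|
| None | within 0.002 | 0.044 to 0.054 |
| Same in both arms | within 0.004 | 0.042 to 0.052 |
| One arm only | −0.020 to −0.049 | 0.058 to 0.075 |
| Opposite in the two arms | −0.043 to −0.108 | 0.064 to 0.170 |

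The lower ends belong to ρ = 0.3 and the upper ends to ρ = 0.7. Under the same dependence in both arms, the arm mean is off by −0.020 to −0.054 log10, in line with the analytic values. The sign reverses if weak rather than strong responders are lost.

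On the fold scale, 10^0.020 = 1.05 and 10^0.049 = 1.12 for one-arm dependence, and 10^0.108 = 1.28 at the extreme. For comparison, the 2-fold difference used for power in section 8.4.2 is log10(2) = 0.301. With 0.75 × 30 = 22.5 observed per arm, the standard error of the contrast is 0.35 × √(2/22.5) = 0.104. The one-arm bias is thus up to about half a standard error, and the extreme about one.

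**With D70 added to the same model:** bias at most 0.004 log10 and type I error 0.044 to 0.061 in every scenario.

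**The case against.** Much of the other side stands.

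- A reader might infer that the univariate model does not relax missing completely at random at all. It does: it allows missingness to depend on arm and baseline covariates, which is a special case of missing at random.
- A reader might infer that the plan has no method using D70. It has one: the repeated-measurement analysis in the same paragraph uses all observed immune data, and ELISpot is a repeated measurement. No sentence ties the primary endpoint to the univariate model alone. However, section 8.5.4 tests arms at a specific time point and makes repeated-measures analyses optional, with a caution about small samples, so the univariate model remains the natural reading for D196.
- The route contrast is biased only if the dependence on D70 differs by arm. The documents do not show that it will. It is conceivable because the trial is open label and section 1.1 reports more local reactions with ID or SC than IM dosing in many earlier studies. But participants are not described as learning their ELISpot results, so dependence would have to run through correlates of the response.
- Baseline predictors may not be empty. The Ad5 titer is measured at screening, and the Protocol expects pre-existing Ad5 immunity to affect response. That D70 is the best predictor is likely but not documented.
- The analysis is secondary, and section 8.4 plans for only 10% missing primary data.

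These points limit the size and likelihood of the problem. They do not explain why an observed, already collected predictor should be withheld from the D196 analysis when the trigger is met.

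**Conclusion.** This is an improvement available at almost no cost, not a demonstrated error. As written, the univariate model in section 8.5.4.1 is valid for the D196 contrast only if missingness depends on arm and baseline covariates; it does not cover missing at random given all observed data.

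Under the assumed inputs, loss that depends on D70 in one arm only moves the contrast by about 0.02 to 0.05 log10, with type I error about 6% to 8%. About 0.1 log10 and 17% requires opposite dependence in the two arms together with a correlation of 0.7. With the same dependence in all arms, the contrast holds and only the arm means are biased.

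The documents do not support concluding that the primary t-test result is wrong, or that route comparisons will be biased. They give neither the D70–D196 correlation nor any evidence on how loss relates to response.

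**What to change.** Add one sentence to section 8.5.4.1, or settle it in the SAP. When the 20% trigger is met, the missing-at-random analysis of the D196 endpoints is the multiple-imputation or longitudinal analysis already planned in that paragraph. It uses arm, baseline predictors including Ad5 titer, and the observed D70 value of the same assay, with the arm contrast read at D196.

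The simpler alternative is to add D70 to the univariate model. Because D70 precedes the boost and follows the same prime in every group, it is not affected by route and is a legitimate covariate. The drawback is that participants with D196 but no D70 would drop out of that model, which imputation avoids.

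The cost is wording and a little programming. Appendix B already schedules ELISpot, flow cytometry and binding ELISA at D70, so no visit, sample or assay is added.
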